## Abstract

**Background:**

Major depressive disorder (MDD) is associated with chronic biases in the allocation of attention and recollection of personal memories. Impaired flexibility in attention and autobiographical memory retrieval is seen to both maintain current symptoms and predict future depression. Development of innovative interventions to reduce maladaptive cognitive patterns and improve cognitive flexibility in the domain of memory may therefore advance current treatment approaches for depression. Memory specificity training and cognitive bias modification techniques have both shown some promise in improving cognitive flexibility. Here we outline plans for a trial of an innovative memory flexibility training programme, MemFlex, which advances current training techniques with the aim of improving flexibility of autobiographical memory retrieval. This trial seeks to estimate the efficacy of MemFlex, provide data on feasibility, and begin to explore mechanisms of change.

**Methods/design:**

We plan a single-blind, randomised, controlled, patient-level trial in which 50 individuals with MDD will complete either psychoeducation (n = 25) or MemFlex (n = 25). After completing pre-treatment measures and an orientation session, participants complete eight workbook-based sessions at home. Participants will then be assessed at post-treatment and at 3 month follow-up. The co-primary outcomes are depressive symptoms and diagnostic status at 3 month follow-up. The secondary outcomes are memory flexibility at post-treatment and number of depression free days at 3 month follow-up. Other process outcomes and mediators of any treatment effects will also be explored.

**Discussion:**

This trial will establish the efficacy of MemFlex in improving memory flexibility, and reducing depressive symptoms. Any effects on process measures related to relapse may also indicate whether MemFlex may be helpful in reducing vulnerability to future depressive episodes. The low-intensity and workbook-based format of the programme may improve access to psychological therapies, and, if encouraging, the results of this study will provide a platform for later-phase trials.

**Trial registration:**

NCT02371291 (ClinicalTrials.gov), registered 9 February 2015.

## Background

Major depressive disorder (MDD) runs a chronic and unrelenting course. While current treatments for depression are effective, rates of relapse are high, with more than 80 % of sufferers experiencing future episodes [1]. Attention has therefore turned to how best to enhance and advance current therapeutic practice in order to reduce relapse. Along with the stereotypical symptom of low mood, depression is associated with a range of cognitive impairments [2]. In particular, depression is associated with fixed, habitual biases in the allocation of attention and recollection of personal memories. Chronic cognitive bias, or reduced cognitive flexibility, is seen to both maintain current symptoms and predict future depression [3, 4]. Development of innovative interventions to reduce maladaptive cognitive patterns and improve cognitive flexibility may therefore advance current treatment approaches for depression [3, 5, 6].

Cognitive flexibility is a key contributor to daily wellbeing. The absence of flexibility is linked to a number of different psychopathologies [7], and is an integral feature of depression [8]. Rigid and automatic cognitive bias is most prominent in attending to and remembering information [9]. When attending to information, depressed individuals demonstrate negative inferences about ambiguous material [6], preferential bias towards negative stimuli [3, 6], and a chronic tendency towards negative attributions of the self and world [10]. When remembering information, depressed individuals demonstrate a lack of flexibility in moving between general and specific personal memories [11] and, subsequently, impaired retrieval of specific memories [4]. Attention and memory biases also appear to combine to produce a bias toward the recall of negative information [12]. As rigid cognitive patterns continue to be observed once depression has remitted [13], a lack of cognitive flexibility is considered a vulnerability factor for future depressive symptoms [6].

Empirical attention has therefore turned to interventions that target cognitive flexibility. Attentional bias has been primarily targeted though cognitive bias modification (CBM) [14]. CBM trains individuals to repeatedly engage with neutral or positive stimuli to reduce the automaticity with which negative information is attended to, thereby reducing negative bias. Originally designed to reduce the tendency towards selective processing of threatening information in anxiety, the technique has begun to be applied to depression-related biases. Meta-analysis demonstrates a moderate effect of CBM in reducing both attention and processing biases in depressed samples [14]. Prior research has also suggested a positive impact of CBM on depressive symptoms (e.g. [15]). Though further research is needed, CBM may hold some promise for targeting attention bias in depressed samples.

Changing the nature of retrieved autobiographical (i.e. personal) memories has been the primary target for memory-based interventions. Autobiographical memories may be recalled as specific memories, and refer to one particular event (e.g. having dinner on my birthday this year), or general memories, which summarise categories of events (e.g. my birthday parties). Depressed individuals consistently demonstrate reduced recall of specific memories in cued retrieval tasks, which in turn predicts depression symptoms up to a year later (for review see [16]). Reduced specificity also reduces everyday skills such as problem solving [17] and the ability to readily imagine future events (which is critical for planning) [18]. Memory specificity training therefore aims to improve access to specific memories by educating the participant about the different types and roles of autobiographical memories, and giving them repeated practice in recalling specific memories.

Current evidence for the likely efficacy of training enhanced specificity is promising. The initial training programme devised by Raes and colleagues [19] improved depressive symptoms in a sample of inpatients in an uncontrolled trial. In the first randomised controlled study, Neshat-Doost et al. [20] also demonstrated that bereaved adolescents who completed 5 weeks of memory specificity training experienced fewer symptoms of depression at 2 month follow-up compared to a control condition. Further, the impact of training on depressive symptoms at follow-up was mediated by improvement in memory specificity. Training has also proved successful in those with post-traumatic stress disorder (e.g. [21]), suggesting potential transdiagnostic effects. There are currently further evaluations of memory specificity training underway (e.g. [22]); however, these initial findings indicate that targeting reduced specificity shows promise in alleviating depressive symptoms.

The bias toward negative memories, and corresponding reduced access to positive memories, has also received some attention in interventions. In depressed samples, negative memories are recalled more often than positive memories [12] which contributes to the pervasively negative view of the self and world [9]. When positive memories are recalled, they are less vivid [23, 24], and have a reduced impact on affect [25, 26]. Recall of positive memories is a key technique in regulating negative affect [27] and, as such, reduced access and quality of positive memories is likely to impact mood regulation. CBM techniques for reducing negative attentional bias have begun to be adapted for memory retrieval in depressed samples, and have been seen to reduce negative generalisation and depressive symptoms [28, 29]. Novel approaches toward bias reduction have also emerged. The Method-of-Loci technique has been successfully used as a mnemonic device to facilitate the recall of elaborated positive memories in depressed samples [30]. Reduction of bias toward negative memories and enrichment of positive memories through the adaptation of existing memory therapeutics is therefore likely to aid cognitive flexibility and, in turn, psychological wellbeing.

In sum, depressed individuals demonstrate cognitive inflexibility in their attention to emotional information, along with retrieval of autobiographical memories. Biases in these cognitive processes can be durable cognitive markers of depression, and are related to symptom severity. Previous interventions have yielded positive results, and suggest that training cognitive flexibility may reduce current symptoms. However, current training techniques could be enhanced to improve treatment effects. For example, it is not only impaired recall of specific memories but also the ability to alternate between specific and general memories that relates to depression symptoms [11]. Improving access to specific memories through memory specificity training may influence flexible movement between memory types; however, further direct training of this skill may more effectively improve cognitive flexibility. In addition, flexibility training could be advanced to simultaneously target both the negative and general memory bias, rather than training these skills through separate programmes. This would reduce treatment duration, more holistically train cognitive flexibility, and potentially achieve greater improvement in depressive symptoms. Finally, cognitive models of depression indicate that improved flexibility may reduce the risk of relapse by improving daily functioning skills such as problem solving and mood regulation techniques. However, mechanisms underlying flexibility training have yet to be comprehensively explored. This proposed trial aims to advance current training practices by addressing each of these issues.

We plan to evaluate a novel cognitive intervention, MemFlex. The MemFlex programme combines CBM techniques and memory specificity training to simultaneously target multiple cognitive biases and thereby improve flexibility in three key areas: 1) reducing bias toward negative information in memory and attention; 2) improving the quality of positive memories by encouraging memory elaboration; and 3) encouraging flexible movement between general and specific autobiographical memories. We compare MemFlex to a psychoeducation control condition in a sample of depressed British adults to establish the efficacy and feasibility of MemFlex. We also provide a preliminary examination of whether MemFlex may impact everyday processes such as problem solving, rumination, and cognitive avoidance, and if changes in these processes may underlie treatment effects. In doing so, we address three key questions. First, does MemFlex improve memory flexibility and reduce depression symptoms? Second, is any improvement superior to that achieved by a psychoeducation intervention? Finally, what are the likely mechanisms mediating any treatment effects? We hypothesise a significant effect of treatment condition on our co-primary outcome variables of depressive symptoms and depression status at 3 month follow- up. Specifically, we predict that participants in the MemFlex condition will exhibit fewer depressive symptoms, and be less likely to meet criteria for a major depressive episode than those in the psychoeducation condition. We also hypothesise that participants in the MemFlex condition will demonstrate increased flexibility in memory retrieval at post-treatment and a greater number of depression-free days at 3 month follow-up, relative to the psycheducation control, as secondary outcomes.

## Methods/design

### Study design

The design is a single-blind, patient-level, randomised controlled trial (RCT) comparing MemFlex to psychoeducation. Each condition will comprise a 4-week programme, consisting of an initial face-to-face session, followed by 4 weeks to complete a self-guided workbook. Participants will be assessed pre-treatment, post-treatment, and at a 3 month follow-up. Upon completion of the 3 month follow-up, those in the psychoeducation condition will be given access to the MemFlex materials. The co-primary outcome measures will be depressive symptoms and diagnostic status at 3 month follow-up.

### Participants and recruitment

We will recruit 25 participants per condition (n = 50) with a primary diagnosis of MDD. Inclusion criteria are age over 18 years and currently experiencing a major depressive episode, as assessed using the Structured Clinical Interview for the Diagnostic and Statistical Manual (DSM)-IV (SCID) [31]. Participants will be excluded if their SCID assessment indicates they are experiencing another mood disorder, psychosis, or current alcohol or substance dependence/abuse. Those with a diagnosed personality  disorder or brain injury (assessed by participant report) will also be excluded.

Participants will be recruited in three ways. First, we will recruit from the community via posters and advertisements. Potential participants who make contact after seeing an advertisement will be sent an information sheet. If consent to contact is given, we will then telephone the individual to complete an initial telephone screening. Second, we will recruit from our department volunteer database, which consists of approximately 300 volunteers who have a history of depression and have expressed a wish to participate in research into the disorder. Those on the database will be emailed the study information sheet, and directed to contact the research team if they would like to participate. Again, those interested in participating will then complete an initial telephone screening. Finally, we will also recruit those from clinical facilities who have given consent to be contacted regarding participation in depression research. Recruitment of these participants will follow the same procedure as our database. Following the initial telephone screening, all eligible participants will be invited to complete a SCID and the pre-treatment assessment.

**Fig. 1 Fig1:**
[figure not shown]
CONSORT diagram

### Interventions

#### MemFlex

The MemFlex programme draws on CBM and memory specificity training techniques [19, 22]. MemFlex is primarily self-guided and covers three key memory skills to reduce autobiographical memory biases associated with depression. These skills are summarized as 'balancing', 'elaboration', and 'flexibility'. The training material is presented over one face-to-face introductory session and eight self-guided sessions. The initial face-to-face session is completed with a researcher at the research centre. In this session the researcher provides an introduction to different memory systems (e.g. working memory versus autobiographical memory), and outlines the importance of autobiographical memory in everyday life. The impact of depression on autobiographical memory is covered, along with the different types of autobiographical memories (e.g. specific, general). The researcher introduces cued–recall tasks which are used throughout the workbook, and guides the participant in completion of these tasks. When understanding of the basic principles is satisfactory, the researcher assists the participant to set a schedule for completion of the workbook over the following 4 weeks. Participants will receive weekly emails during this period encouraging them to complete the workbook. They will also receive a telephone call from a team member at the beginning of week 3 to check progress, and clarify any difficulties with the workbook material.

Session 1 of the workbook reviews the material covered in the face-to-face session, and introduces the 'balancing' skill. Balancing refers to improving access to both specific and general memories of neutral and positive valence. Following a description of the skill, the participant is given practice retrieving positive and neutral memories. As depression is consistently associated with prolific retrieval of negative and general autobiographical memories, we focus on improving access to other autobiographical memories. Session 2 introduces 'elaboration'; that is, enriching the detail of recalled memories and improving access to the emotion attached to the memory. Again, once the skill is introduced, the participant is given practice elaborating positive memories. Session 3 consolidates previous skills, before 'flexibility' is introduced in Session 4. The flexibility skill helps participant to move between specific and general memories. Sessions 5 to 8 give participants practice in using the different skills, and aim to develop automaticity of the retrieval processes. In addition to completing the sessions in the workbook, individuals are required to practice generative memory retrieval multiple times a day.

We have previously evaluated the feasibility of MemFlex with a group of 38 individuals with a history of MDD but currently in remission. Based on feedback from those individuals, the workbook was refined, and expanded from six to eight sessions. The revised workbook was then subjected to a final feasibility evaluation with three individuals with a current diagnosis of MDD. No further changes were made.

### Measures

#### Primary outcomes

The co-primary outcomes are depressive symptoms at 3 month follow-up, as reported on the Beck Depression Inventory II (BDI-II), and diagnostic status at 3 monthfollow-up, which will be measured using the Longitudinal Interval Follow-up Evaluation of the SCID [31].

### Secondary outcomes

Of secondary interest is the number of depression-free days since post-treatment, which will be measured at 3 month follow-up using the Longitudinal Interval Follow-up Evaluation of the SCID [31]. We are also interested in the flexibility of autobiographical retrieval at post-treatment, measured using the Autobiographical Memory Task (AMT) with Alternating Instructions [11]. As MemFlex aims to improve the flexibility with which an individual can move between specific and general memories, we used an alternating instruction AMT (AMT-AI), rather than the traditional AMT [32], which indexes the retrieval of specific memories alone. The AMT-AI requires participants to retrieve specific memories to a block of six cue words, general memories for a block of six cues, and finally a block of twelve cues in which the individual must alternate between retrieval of specific and general memories. Order of the specific and general blocks is randomised between participants. Cues are of positive, negative, and neutral valence, and are also randomised to block. The number and proportion of correct responses is calculated for each block (i.e. specific, general, alternating). The total number of correct responses and the number of correct responses in the alternating block will be used as the main outcome variables.

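### Memory flexibility has two unranked, overlapping main scores, and half the cues in one of them require no alternation; the alternating-block score should lead (minor)

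*Protocol article*

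**What the plan says.** The abstract lists memory flexibility as one item: "The secondary outcomes are memory flexibility at post-treatment and number of depression free days at 3 month follow-up". The Background likewise gives one directional hypothesis, that "participants in the MemFlex condition will demonstrate increased flexibility in memory retrieval at post-treatment".

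The Secondary outcomes section explains why the alternating-instruction version of the memory task was chosen: "As MemFlex aims to improve the flexibility with which an individual can move between specific and general memories", this version was used "rather than the traditional AMT [32], which indexes the retrieval of specific memories alone". The task asks participants to "retrieve specific memories to a block of six cue words, general memories for a block of six cues", and then gives "a block of twelve cues in which the individual must alternate between retrieval of specific and general memories". Number and proportion correct are calculated for every block. The section then names two leading variables: "The total number of correct responses and the number of correct responses in the alternating block will be used as the main outcome variables". It does not say which comes first or what to conclude if they disagree.

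The Statistical analysis plan section assigns independent-samples t-tests to the secondary outcomes and allows baseline differences as covariates where appropriate. It states no significance level and no multiplicity rule.

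**The concern.** By the article's own rationale, the target is movement between specific and general memories. Within the two single-instruction blocks nobody has to move between types, yet those blocks supply half of the possible total score. Two consequences follow.

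- **Attribution.** If training improved only recall under a single instruction, the total would rise and could be presented as improved flexibility. The Background treats alternation as a skill beyond specific recall, and training it directly is the programme's claimed advance.
- **Two estimates for one hypothesis.** Unless training acts on all blocks in just the right proportion, the standardised effects on the total and on the alternating block differ. The article says the trial should supply estimates to guide later sample sizes, so it matters which score gives the estimate. The two tests also overlap, which gives two chances of a positive finding on one hypothesis.

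**Working it through.** **Inputs from the article:** 6 specific, 6 general and 12 alternating cues; 25 participants per arm; t-tests for secondary outcomes.

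**Inputs assumed, because the article gives none:** two-sided 0.05 per test; block SDs of 2.5 (alternating), 1.5 (specific) and 1.5 (general); a common between-block correlation r of 0.3 to 0.5; standardised effect d = 0.6 on the alternating block. The article states no power, effect size or SD for this outcome, so there is no planned figure to reproduce.

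**1. Composition of the total.** (6 + 6)/(6 + 6 + 12) = 12/24 = 50% of the maximum score. The share of an observed score depends on accuracy in each block.

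**2. SD of the total.** Variance = 2.5² + 1.5² + 1.5² + 2r(2.5×1.5 + 2.5×1.5 + 1.5×1.5) = 10.75 + 19.5r.
- r = 0.3: variance 16.6, SD 4.07.
- r = 0.5: variance 20.5, SD 4.53.

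**3. Effect on the total.** Let the effect in each single-instruction block be k times that in the alternating block, in SD units. Then d_total = 0.6 × (2.5 + 3.0k)/SD_total.

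| Scenario | r | d on total | Power, total | Power, alternating |
|---|---|---|---|---|
| Only alternation improves (k = 0) | 0.3 | 1.5/4.07 = 0.37 | 25% | 55% |
| | 0.5 | 1.5/4.53 = 0.33 | 21% | 55% |
| All blocks improve equally (k = 1) | 0.3 | 3.3/4.07 = 0.81 | 80% | 55% |
| | 0.5 | 3.3/4.53 = 0.73 | 71% | 55% |

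Power is from the noncentral t distribution with 48 degrees of freedom.

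**4. Break-even.** The total is the weaker score when (2.5 + 3.0k)/SD_total < 1, that is, when k < (SD_total − 2.5)/3.0. This gives 0.52 at r = 0.3 and 0.68 at r = 0.5.

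**5. Sensitivity to the SD assumption.** Now give the alternating block and the combined single-instruction blocks equal SDs and correlation ρ, so that d_total = d(1 + k)/√(2 + 2ρ). With d = 0.8 and ρ of 0, 0.5 and 0.7 (normal approximation), power on the alternating block is 81%. On the total it is 52%, 37% and 34% at k = 0, and 98%, 90% and 87% at k = 1. Break-even k is 0.41, 0.73 and 0.84. The pattern is the same.

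**6. Two overlapping tests.** Two independent tests would give 1 − 0.95² = 9.75%. These are not independent. Under the step 2 assumptions the correlation of the alternating score with the total is (6.25 + 7.5r)/(2.5 × SD_total), which is 0.83 at r = 0.3 and 0.88 at r = 0.5. The bivariate-normal chance that at least one is significant under no effect is then 7.6% and 7.2%. Under step 5 it runs from 8.3% (ρ = 0) to 6.8% (ρ = 0.7).

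**7. Consequence for later planning.** At 80% power, n per arm ≈ 2(1.96 + 0.84)²/d² = 15.7/d². For d = 0.6 this is 15.7/0.36 ≈ 44. For d = 0.35, midway between the two k = 0 values, it is 15.7/0.1225 ≈ 128.

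**The case against.** The strongest reply is that dilution cannot be taken for granted. The programme's first workbook session trains a different skill: "Balancing refers to improving access to both specific and general memories of neutral and positive valence". The flexibility skill is introduced only in session 4, and sessions 5 to 8 practise the different skills. Gains in the single-instruction blocks are therefore an expected effect of the programme, and step 3 shows the total is then the more sensitive score. This stands, and any statement about power has to show both cases.

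A reader might also infer that half of the total does not measure flexibility at all. The documents do not support that. The complaint about the traditional task is that it covers specific recall only, whereas this total also covers general recall and alternation. The Background names three areas in which flexibility is to improve, and movement between memory types is one of them. Retrieving either type on request is a defensible broader index, although it is not the reason the article gives for choosing the task.

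A reader might infer a serious error-rate problem. The inflation is small because the scores overlap, no significance level is stated, the co-primary outcomes are elsewhere, and the stated aim is estimation. The scores for each block are also calculated under the plan, so a gain confined to specific recall would be visible if they are reported.

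Finally, ranking two scores from one task is often left to a statistical analysis plan, and one may exist that does so. That is fair as regards a rule for disagreement. It does not remove the point, because the article itself gives both scores main status for a hypothesis stated in the singular.

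**Conclusion.** The point holds in a limited form. The article fixes two unranked, nested main variables for one flexibility hypothesis, and exactly half the cues in one of them need no alternation. The two scores can yield different estimates, with nothing in the article to say which answers the hypothesis.

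The total can weaken an alternation-specific effect, but this is conditional: it does so only if the effect in the other blocks is below about 0.52 to 0.68 of the alternating effect under the main assumptions. Above that the total has more power. All SDs, correlations, effect sizes and the 0.05 level are assumptions; only the cue counts and the arm size come from the article. The case for the alternating block as lead therefore rests on its match to the article's stated target, not on a general gain in power. Severity is minor: this is a secondary outcome in an exploratory trial, and the co-primary outcomes are unaffected.

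**What to change.** Name the number correct in the 12-cue alternating block at post-treatment as the leading flexibility variable. Analyse it by ANCOVA on its pre-treatment score in place of the unadjusted t-test. Report the total, specific-block and general-block scores as supportive, so that readers can see whether any gain is particular to alternation.

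The cost is wording and one model specification. The Data collection section has all measures taken at pre- and post-treatment, and all block scores are already calculated, so no new data are needed. Fixing the baseline covariate in advance also removes the choice left open by adjusting only where appropriate; it reduces residual variance to the extent that pre- and post-treatment scores correlate, which the article does not quantify.

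The downside is that if training lifts all blocks equally, the leading test gives up power: 55% against 71-80% on the total, before baseline adjustment and under the assumptions above. If the trial team prefers the broader construct, the alternative is to lead with the total, define flexibility accordingly, and say how a disagreement with the alternating score will be interpreted.
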